Approximately 20% of the US workforce participates in shift work (12) including almost one-third of full-time nursing professionals (2). Nineteen to 29% of shift workers are thought to experience fatigue (13). Studies comparing shorter shifts (8 hr) to longer shifts (12 hr) found that while some workers preferred the benefits of the longer shift (i.e. shorter work week), fatigue and decreased alertness was experienced near the end of the shift (14). One large cohort study including female nurses found shift work, particularly night duty (*p*<0.001), to be the most important predictor of fatigue (15).

- - 1. DEFINING FATIGUE

Fatigue is a subjective and heterogeneous experience, making an exact definition difficult to capture. Since the proposed study intends to measure work-related fatigue, we will refer to fatigue as that outlined by the Canadian Centre for Occupational Health and Safety: the state of feeling very tired, weary or sleepy resulting from insufficient sleep, prolonged mental or physical work, or extended periods of stress or anxiety (16).

- - 1. TREATMENT OF FATIGUE

Work-related fatigue may be best-managed by better regulation of working hours, especially for those involved in shift work. In Canada and the US, nursing work hours are self-regulated and nurses are expected to use professional judgment to determine whether fatigue might interfere with their performance and, if so, to refrain from practising. Although there is general consensus that a reduction in working hours is necessary, there is little incentive to do so.

A variety of educational and administrative interventions have been employed to help health care personnel adapt to working shifts however, these are difficult to implement on an already strained health care system. There is currently no cure or specific medical treatment for fatigue. Treatment, if used, is aimed to reduce symptoms of fatigue such as loss of memory and concentration, headache, sleep problems and exhaustion. Such treatments may include: anti-anxiety medications, antidepressants, and dietary changes. However, some medications, such as antidepressants or stimulant medications may have unintentional consequences such as dependency (17).

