**Each *R.rosea* capsule will contain 182.0 mg of the product.** Participants will be asked to take two capsules of the trial medication at the start of their wakeful period each day. Since fatigue is a subjective symptom, participants will be asked to self-determine their need for a second dose of the trial medication within the four hour period after the initial dose. The second dose willbe one capsule~~;~~ the daily MYMOP will ask participants to record the number of capsules ingested in the past 24 hours.

***Dose & duration justification:*** Since the majority of previous trials that found significant effects assess long-term, rather than acute supplementation of *R. rosea*, this trial will examine efficacy over a similar duration yet with an aim to overcome limitations of previous studies. **Based on dose and duration information previous studies of** R. rosea **for mental and physical performance (Table 2), the maximum dose of** R. rosea **without adverse effects is 1500 mg over three days (short-term supplementation). The maximum dose that has been safely used in long-term supplementation is 680 mg standardized to 3.0% rosavins for a six week period. The *R.rosea* formulation being used in this trial has been standardized to contain 2.8% rosavins; therefore the equivalent maximum daily dose for this study is 546 mg.**

- 1. **Treatment allocation**

**Partcipants will be assigned to a treatment group (either *R.rosea* or placebo) according to a computer generated randomisation scheme produced by our data management team at the Epidemiology Coordinating and Research Centre at the University of Alberta.** Sampling will be stratified by night vs. rotational shift workers and a permuted block randomization technique will be used with permuted block sizes of 4. Although the nursing profession is dominated by females, there has been no consistent association between fatigue and gender and therefore randomization will not be stratified by gender.

**The Investigator will be supplied with individual code-break envelopes for each patient, containing details of the patient’s treatment. Sealed copies of the randomisation code will also be retained by the study pharmacist, [name]** [name]**.**

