1. STATISTICAL CONSIDERATIONS
   1. SAMPLE SIZE JUSTIFICATIONS

Lack of an appropriate, standard, valid tool to measure fatigue has been a barrier to high quality fatigue research. Previous R. rosea has suffered the consequence of this. Since no previous studies of R. rosea used a validated outcome measure or presented data in a manner on which to base sample size, sample size was calculated using the effect size from a comparable study of ginseng on fatigue (a comparable product from the same therapeutic class, i.e. adaptogen) (46). Using a two sided, two-sample t-test, a sample size of 64 participants achieves 90% power to detect an absolute mean difference of 6.5 on the RAND-36 vitality subscale between those randomized to receive R. rosea versus placebo at 0.05 level of significance (two-sided test). Assuming a drop-out rate of 40%, the sample size is increased to 90.

- 1. STATISTICAL ANALYSIS

Analysis will be conducted by the Epidemiology Coordinating and Research (EPICORE) Centre at the University of Alberta.

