All primary analyses will apply the intention to treat principles. All statistical tests are two-sided and tests will be evaluated against 0.05 level of significance. Estimates and corresponding 95% confidence intervals will be reported. The RAND-36 vitality subscore will be used as the primary indicator of the efficacy of *R.rosea*. To test the main hypothesis of the effects of *R.rosea* in reducing fatigue of nurses involved in shift work, the mean change from baseline to six weeks of the vitality subscore using RAND-36 will be compared between the *R.rosea* and placebo groups. This 2-sample t-test will be supplemented by additional analyses using rate of change outcome measure. Linear mixed model will be employed to test changes in the intercept and slopes of the treatment groups. This type of modelling accounts for the variability and correlatedness of the observations on the same participant. Despite the tendency of participants to miss testing occasions, the mixed model analyses can still evaluate any trajectories of change. Missing data will be checked for randomness and correlation with adverse events will be explored. Since RAND-36 vitality subscore is not validated for use in this specific population, correlatedness between it and a visual analogue scale for fatigue (VAS-F) will be tested. In addition, correlatedness between ACI, will be tested against the primary outcomes in order to establish further evidence of validity. RAND-36 physical and mental component scores will be analysed by testing their mean change from baseline to day 42 between treatment groups, as a secondary outcome. Mixed model analyses will be applied for testing change for VAS-F, RAND-36, ACI and MYMOP. Side by side graphs of the rates of change between treatment groups will be plotted at the exploratory and final stages of analysis. Examination of the effect of the covariates - concurrent medication, dose-related change, sleep, alcohol use and impact of specific rotation (rotating vs permanent shift-work), age and marital status will be analyzed using linear mixed regression models as secondary outcomes. SAS 9.1 (Cary, N.C.) will be used for data management and statistical models. SPSS (Michigan) or Splus/ R will be used for supplemental graphs.

Adverse events will be monitored daily. Rates of adverse events will be compared between the two groups using the chi squared test at baseline, day 21 and day 42 measurements.

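### The primary t-test on change in vitality is valid but inefficient: it fixes the baseline slope at 1 and omits the shift-type factor used to stratify randomisation

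*Protocol*

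**What the plan says.** Protocol section 8.2 takes the RAND-36 vitality subscore as the primary measure of efficacy and compares its mean change from baseline to six weeks between the two arms. The test is named in the next sentence, and everything else is supplementary: "This 2-sample t-test will be supplemented by additional analyses using rate of change outcome measure". No covariate is attached to it. The significance rule is "All statistical tests are two-sided and tests will be evaluated against 0.05 level of significance".

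Both candidate covariates are available. Section 7.1.1 schedules the instrument at baseline and then weekly to day 42. Section 6.3 states: "Sampling will be stratified by night vs. rotational shift workers and a permuted block randomization technique will be used", with blocks of 4. Shift type reappears in section 8.2 only as one of several covariates in linear mixed models labelled secondary. Baseline vitality is not in that covariate list.

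On size, section 8.1 says "a sample size of 64 participants achieves 90% power to detect an absolute mean difference of 6.5 on the RAND-36 vitality subscale" and then "Assuming a drop-out rate of 40%, the sample size is increased to 90". It gives no SD and no correlation between baseline and week 6.

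**The concern.** A change score sets the coefficient of baseline to exactly 1. When baseline and week 6 are imperfectly correlated and have similar variances, the best coefficient is rho, which is below 1. Forcing it to 1 adds noise. It also means that, in any one trial, a chance difference in baseline means carries into the estimate through regression to the mean.

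Leaving out the stratification factor is a second possible loss. The arms are balanced on shift type by design, so if shift type predicts the outcome, an analysis that ignores it overstates the standard error.

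What is at stake is the width of the primary confidence interval and the power of a small trial. Both covariates are recorded anyway.

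**Working it through.** **Inputs.** From section 8.1: difference 6.5, power 90%, 64 evaluable, 40% drop-out, 90 enrolled. From section 8.2: alpha 0.05, two-sided. Allocation is 1:1 (section 6.6 tells participants they have a 50% chance of active product). I read 64 as the total, 32 per arm. Assumed, because not stated: the SD, and rho over 0.3 to 0.9.

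**1. The plan's own figures.** The 90% cannot be reproduced independently without an SD. Solving the noncentral t for 32 per arm, 6.5 points and 90% power gives SD = 7.90, a standardised difference of 6.5/7.90 = 0.823. I take this as the SD of change, since change is what the primary test analyses. For drop-out, 64 x 1.4 = 89.6 gives the stated 90, but keeping 64 after 40% loss needs 64/(1 - 0.4) = 107. Ninety enrolled with 40% lost leaves 90 x 0.6 = 54.

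**2. Unadjusted t-test.** SE = 7.90 x sqrt(2/n per arm). At 32 per arm power is 90.0% by construction. At 27 per arm SE = 2.15 and power is 84.3%, a loss of 5.7 points.

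**3. Variance ratio.** Let s be the common SD at baseline and week 6.
- Change score: variance 2s²(1 - rho).
- ANCOVA: residual variance s²(1 - rho²).
- Ratio: (1 - rho²)/[2(1 - rho)] = (1 + rho)/2.

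This is below 1 for every rho below 1. It leaves out the small cost of estimating the slope when baselines differ by chance, which matters only when rho is close to 1.

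**4. ANCOVA power**, with SD 7.90 x sqrt((1 + rho)/2) and two error degrees of freedom removed:

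| rho | Variance ratio | Standard error smaller by | Power, 54 completers | Power, 64 completers |
|---|---|---|---|---|
| t-test on change | 1 | – | 84.3% | 90.0% |
| 0.3 | 0.65 | 19% | 95.7% | 98.0% |
| 0.5 | 0.75 | 13% | 92.9% | 96.3% |
| 0.7 | 0.85 | 8% | 89.6% | 94.0% |
| 0.9 | 0.95 | 3% | 86.1% | 91.4% |

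**5. Chance imbalance.** Given a baseline difference D between arms, the change-score estimate shifts by about -(1 - rho)D. At 27 per arm the standard error of D is sqrt(2/27) = 0.27 baseline SDs. At rho = 0.5 the baseline SD is 7.90/sqrt(2 x 0.5) = 7.90, so an imbalance of one standard error moves the estimate by 0.5 x 0.27 x 7.90 = 1.1 points, against a target of 6.5.

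**6. Does adjustment make up for the drop-out arithmetic?** ANCOVA at 54 returns to 90% power when rho is about 0.67 (normal approximation: 2 x 54/64 - 1 = 0.6875). At rho = 0.7 it gains 89.6 - 84.3 = 5.3 points, less than the 5.7 lost. If the stratum explained an assumed 2%, 5% or 10% of residual variance, the break-even would move to about 0.71, 0.76 or 0.86.

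**7. Other readings.** If 64 is per arm (54 per arm completing), the t-test has 84.5% and the break-even is about 0.68. If 7.90 is the SD of a single score, power at 54 completers goes from 70.8% to 87.5% at rho 0.3, from 84.3% to 92.9% at 0.5, and from 96.9% to 98.6% at 0.7.

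**The case against.** The strongest reply is that nothing here is an error. Under randomisation the t-test on change is valid and unbiased, and it is the kind of test on which the sample size was based. That stands: the point concerns efficiency and sensitivity to chance imbalance.

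A second reply is that the mixed models already bring in shift type. They do, but only as supplementary or secondary analyses, so the primary estimate and its interval are unchanged.

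Third, attrition may be low. Section 7.1.3 does not expect many withdrawals, and evaluable numbers could reach 90. With SD 7.90 the unadjusted test has 93% power at 72, 95% at 80 and 97% at 90; it falls below 90% only when drop-out exceeds 1 - 64/90 = 29%. The absolute gain then shrinks, but the variance ratio does not depend on attrition.

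Three stronger readings are tempting and should be resisted:
- **That the primary test ignores baseline.** It subtracts baseline; the weakness is the fixed slope.
- **That omitting the stratum must inflate the standard error.** Section 1.1.3 cites a cohort that found shift work, particularly night duty, "to be the most important predictor of fatigue". Every participant here works shifts, no effect size for permanent nights against rotation is given, and a stable difference in level would cancel in a change score.
- **That adjustment recovers more power than the drop-out error loses.** This depends on rho being below about 0.67 or on a prognostic stratum, and the protocol supplies neither figure.

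**Conclusion.** The point holds as one of efficiency. The protocol commits its primary inference to an unadjusted comparison of change when a baseline-adjusted analysis from the same data would be more precise over the whole assumed range. The gain with 54 completers is about 11 power points at rho 0.3, 9 at 0.5, 5 at 0.7 and 2 at 0.9; with 64 completers it is about 8, 6, 4 and 1.

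These sizes rest on a back-solved SD of 7.9 taken as the SD of change, equal variances at baseline and week 6, and an assumed rho. The direction does not depend on the SD. Any extra gain from the stratum depends on whether shift type predicts week-6 vitality after baseline adjustment, which the documents do not show. The change is worth making but is not needed for the trial to be valid.

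**What to change.** In section 8.2, define the primary analysis as ANCOVA of day-42 vitality on treatment, baseline vitality and randomisation stratum (night or rotating shift), reporting the adjusted difference with its 95% confidence interval. Keep the unadjusted t-test on change as a supportive analysis. Settle this before unblinding, so that the covariates cannot be chosen with results in view. In section 8.1, state the SD, whether it refers to change or to a single score, and the assumed rho.

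The cost is a sentence or two and two degrees of freedom; no new data are needed. Correct the drop-out inflation separately (107, not 90): covariate adjustment neither replaces missing participants nor deals with bias from drop-out.

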Another RCT conducted in Russia evaluated the effect of two different single doses of *R. rosea* on mental fatigue in 121 male military cadets (19-21 years) (31). Subjects were randomized to take 370 mg or 555 mg of *R. rosea (s*tandardized to 2.4% salidroside)or placebo. A non-treatment group was also included, however subjects were not randomized into this group and comparisons against this group is not considered when drawing conclusions. The intervention was taken at 4:00am while participants were on an overnight shift (starting at 6:00pm). Capacity for mental work, measured using a fatigue index of unknown origins, and with no evidence of its psychometric properties, and pulse pressure and rate were evaluated before night duty and one hour after taking the study medication. A self-report questionnaire evaluating general well-being was completed after taking the study medication. The fatigue index was comprised of three parameters: visual perception, short-term memory and perception of order. Improvements in favour of both doses of *R. rosea* were apparent in the fatigue index (*p*<0.001); no significant differences between groups occurred for other outcomes. The method of randomization was unclear and similar to the previous study, the outcome measure does not appear to be validated.

The findings from the above studies are not without major methodological flaws – inappropriate outcome measurement tools and inappropriate analysis approach. The assessment of efficacy of *R.rosea* for fatigue-alleviation in shift-workers would benefit from a well-designed, rigourously conducted RCT.

- - 1. IS RHODIOLA SAFE FOR USE IN THIS POPULATION?

Out of 446 subjects examined in the 11 included clinical studies of physical and mental fatigue, five adverse events were mentioned in three studies. Two subjects on 200 mg of *R. rosea* over a 4-week period each experienced a minor and serious headache (34); one subject on placebo over a 2-day treatment period experienced a minor headache and another had insomnia (29). Another subject on placebo experienced hypersalivation (31). There appear to be few side effects associated with *R. rosea* supplementation; those identified are of a mild nature.

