**The following interventions will be supplied:**

1. ***Rhodiola rosea* extract standardized to2.8% rosavins (**29.0 % microcrystalline cellulose, 0.5% Silicon dioxide
2. **Placebo (**95% microcrystalline cellulose, 0.5% Silicon dioxide)

**Both interventions will be encapsulated in gelatine capsules, which are an animal-based product, and will look identical. Medications will be packaged in identical bottles labelled according to the participants’ randomization code.**

Development of the both interventions will be undertaken by [name] [name], a pharmacist and assistant professor in the Faculty of Pharmacy and Pharmaceutical Sciences at the University of Alberta. [name], will store all trial medications (*R. rosea* and placebo) in a secured storage facility until recruitment. Study medication will then be given to the study nurse for dispensing at time of enrolment; medication will be stored under lock and key accessible only by the study nurse until time of dispensing.

- 1. Treatment regimen

The trial will begin on the day that subjects start their clinical rotations and end 6 weeks later. Subjects will be instructed to take two to four capsules of the trial medication per 24 hour period (see section 6.2). All outcomes will be measured at baseline (Day 0) and at the end of the trial period (week 6). The project coordinator will phone participants on the day(s) leading up to their baseline assessment to remind them to complete their questionnaires and ensure they are comfortable with the study procedures. The primary outcome and two secondary outcomes will be measured again at the end of each week; all other outcomes will be measured daily (see section 7). Subjects will be prompted to report adverse events daily during the trial period and at the end of their clinical rotation four weeks after completion of the trial. During the trial period, the study nurse will phone participants in week 2 and week 5to remind them to complete their questionnaires and to inquire about adverse events (see section 7.1.2).

- 1. DOSE AND DURATION

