**The code for a patient will only be opened in an emergency, when it is necessary for a patient’s treatment to be disclosed. If a code is broken the investigator will inform the Study Director/Monitor and document the details of the reason in the patient’s case report forms.**

- 1. ALLOCATION CONCEALMENT

Participants will receive a sealed, serially-numbered opaque bottle containing the study medication or placebo depending on their randomised group assignment. They will be provided a six-week supply of their assigned study medication.

- 1. BLINDING

**The placebo capsule will have the same appearance, volume, weight, odour and taste as the *R.rosea* product so that neither the participant nor trial personnel know who is receiving which medication. The effectiveness of the blind will be assessed at the beginning of the study after a single dose via the MYMOP on Day 1. Participants will be asked to guess which medication they think they were allocated to.**

- 1. **CO-INTERVENTION AND CONTAMINATION**

**Since stimulant medications have been identified as potentially hazardous to combine with *R.rosea*, subjects being recruited will be considered ineligible for the trial if they are using such medication. As part of their daily questionnaires, participants will be asked to record any medication used (prescription, over-the-counter, or natural health product) and quantity of caffeine and alcohol consumption in the past 24 hours to ensure that important co-variables can be considered in the final analysis. These questions will be administered as part of the daily MYMOP assessment.**

**From the start of the treatment, participants will be advised not to take any rhodiolaor ginseng preparations for the duration of the trial so that only the *R. rosea* treatment will influence trial outcomes. Furthermore, they will be informed that there is a 50% that they may be receiving *R.rosea*, the dose of which is being in this trial is the highest that has been supported by evidence of safety, and cautioned that they would therefore not want to “double-dose” themselves.**

- 1. **ACCOUNTABILITY OF TRIAL MEDICATION**

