4. ***Adverse Event Monitoring:*** The daily MYMOP questionnaire has been adapted to query the participant on adverse events within the last 24 hours. A daily report of this item will be sent to the project coordinator once every 24 hours; if adverse events are reported, the study nurse will be notified to follow-up with the participant(s) by phone within 24 hours. For participants completing paper forms, the study nurse will follow-up once per week via phone call to collect information on adverse events. Nurses will record the nature, severity and duration of the adverse event(s). When serious adverse events are reported (i.e. those warranting physician visits or hospitalization), the study nurse will notify the data and safety monitoring board (DSMB). The DSMB will consist of a clinician, a trial methodologist and someone with natural health product expertise who are independent of the trial. In the event of an adverse event, the study nurse together with the qualified investigator may remove a participant from the trial. If the event(s) warrant it, the DSMB is empowered to stop the study prematurely**.** Subjects will also be contacted by phone once every 2 weeks by the study nurse to be queried about adverse event(s) that were not reported. Participants not participating in online electronic data collection will be asked to contact the study nurse within 24 hours of an adverse event occurring. All adverse events will be followed by the study nurse until resolution of baseline status is achieved or until the completion of the trial (i.e. when ethics approval has expired). We will ensure that Health Canada is informed of all serious adverse events within one week of occurrence.

Adverse events are defined as:

- Any untoward medical occurrence in a patient or clinical investigation subject administered a pharmaceutical product and which does not necessarily have to have a causal relationship with this treatment.

Serious adverse events are defined as:

- any untoward medical occurrence that at any dose:
  - results in death
  - is life-threatening, (NOTE: The term "life-threatening" in the definition of "serious" refers to an event in which the patient was at risk of death at the time of the event; it does not refer to an event which hypothetically might have caused death if it were more severe.)
  - requires inpatient hospitalisation or prolongation of existing hospitalisation,
  - results in persistent or significant disability/incapacity

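### Section 8.2 compares adverse events only at the baseline, day 21 and day 42 measurements: read literally, 2 of 42 on-treatment days plus one pre-treatment test

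*Protocol*

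**What the plan says.** The analysis rule is in section 8.2: "Rates of adverse events will be compared between the two groups using the chi squared test at baseline, day 21 and day 42 measurements". The sentence just before it reads: "Adverse events will be monitored daily". No other between-arm comparison of adverse events is stated. Their only other analytic use is to explore whether missing data are related to them.

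On collection, section 7.1.2 (Adverse Event Monitoring) says: "The daily MYMOP questionnaire has been adapted to query the participant on adverse events within the last 24 hours". Section 6.1 gives the schedule: "Subjects will be prompted to report adverse events daily during the trial period and at the end of their clinical rotation", the latter falling four weeks after treatment ends. On timing, section 6.1 says: "The trial will begin on the day that subjects start their clinical rotations and end 6 weeks later". It places baseline at Day 0. The first questionnaire after dosing is the one for Day 1, as section 6.5 shows: "The effectiveness of the blind will be assessed at the beginning of the study after a single dose via the MYMOP on Day 1".

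On withdrawal, section 7.1.2 withdraws anyone with a serious adverse event, and section 7.1.3 lists adverse events, serious or not, among the withdrawal reasons. Section 7.1.3 also says that those who withdraw are encouraged to complete the assessments of the final follow-up.

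**The concern.** The comparison does not match the data collected. A questionnaire with a 24-hour look-back measures one day, so a test at the day 21 or day 42 measurement sees only what was present on that day. Events that began and resolved on the other 40 days would be recorded but would not enter any comparison.

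One of the three tests is made before treatment. At Day 0 any difference between randomised arms is chance, so that test says nothing about the product.

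There is also a selection issue. A participant who stops in week 1 because of an adverse event may not complete the day 21 questionnaire. A late questionnaire with a 24-hour look-back would not recover the event that caused the withdrawal.

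Section 11 says the trial will provide evidence on safety as well as efficacy. A comparison limited to two days would rest on very few events and would lean towards participants who tolerated the product.

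**Working it through.** The protocol states no adverse event rate, power or sample size for this comparison, so there is no figure to reproduce. The check counts how much of the treatment period the stated time points cover.

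**Inputs from the protocol**
- Treatment period: 6 weeks = 42 days (6.1).
- Look-back of each questionnaire: 24 hours (7.1.2).
- Tested time points: baseline (Day 0), day 21, day 42 (8.2).
- Planned total: 90 (8.1), so 90/2 = 45 per arm before drop-out.

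**Step 1: days covered.** Two on-treatment questionnaires of one day each cover 2/42 = 4.8% of on-treatment days. The other 40/42 = 95.2% lie outside.

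**Step 2: share of events captured.** Assume onset is equally likely on each of days 1 to 42 and an event lasts L consecutive days. It is present on day d if it starts on one of the L days from d − L + 1 to d. For L up to 21 the sets of start days for d = 21 and d = 42 do not overlap, so the share captured is 2L/42.

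| Assumed duration L (days) | Start days captured | Share |
|---|---|---|
| 1 | 2 of 42 | 4.8% |
| 2 | 4 of 42 | 9.5% |
| 3 | 6 of 42 | 14.3% |
| 7 | 14 of 42 | 33.3% |
| 14 | 28 of 42 | 66.7% |
| 21 | 42 of 42 | 100% |

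The result depends heavily on duration. The shares are per episode; a participant with repeated episodes is more likely to be counted.

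**Step 3: what this does to the counts.** As an illustration only, assume 42-day risks of 20% and 50%, a constant daily hazard, one-day events, 45 per arm and no drop-out. The daily risk is 1 − (1 − risk)^(1/42).
- Risk 20%: 1 − 0.80^(1/42) = 0.0053, so 45 × 0.0053 = 0.24 participants expected with an event on a given day.
- Risk 50%: 1 − 0.50^(1/42) = 0.0164, so 45 × 0.0164 = 0.74 participants.
- Counted from first dose to day 42: 45 × 0.20 = 9 against 45 × 0.50 = 22.5 participants.

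Even a large difference in cumulative risk would leave fewer than one expected case per arm on a single tested day.

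**Step 4: is the test itself at fault?** The exact size of Pearson's chi-squared test at 45 per arm is 0.010, 0.049, 0.059 and 0.054 for a common true rate of 2%, 5%, 10% and 20%. It is conservative or close to 0.05, so the time points are the main fault.

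**Step 5: the baseline test.** Baseline is Day 0, and the Day 1 questionnaire is the one that follows a single dose. The Day 0 test is pre-treatment whichever way the sentence is read.

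**The case against.** The strongest objection is that the sentence may mean cumulative rates up to day 21 and day 42. It speaks of rates, it follows directly on the statement about daily monitoring, and weeks 3 and 6 are marked in the design schematic. On that reading all reported on-treatment events count and the losses in Step 2 vanish. A reader might infer that the plan certainly discards about 95% of events and will understate harm. The document does not support that as a certainty. What stands is that the text refers to measurements at time points, lists baseline among them and defines no accumulation window, so the literal reading is a point measurement.

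A reader might also infer that everyone who stops early because of an adverse event is absent from both time points. That is too strong: section 7.1.3 encourages those who withdraw to complete the final assessments and records the reason for withdrawal. They may have no record; it is not certain.

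A third tempting inference is that events up to day 70 should have been tested too. After day 42 they are not collected daily but queried at the end of the rotation, so such a comparison would depend on recall and attendance. Leaving it untested is a reasonable choice.

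The literature count in section 1.2.3 ("Out of 446 subjects examined in the 11 included clinical studies of physical and mental fatigue, five adverse events were mentioned in three studies") is weak evidence that few events will occur here. It counts what earlier trials mentioned, and section 1.2.3 itself warns that reporting for such products may be incomplete. The point does not depend on it.

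Finally, safety details are often left to a statistical analysis plan. That would excuse silence, but this protocol names the test and the time points.

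**Conclusion.** The point holds in a limited form. As written, section 8.2 ties the adverse event comparison to single-day measurements that cover 2 of 42 on-treatment days (4.8%). Under uniform onset it would capture between about 5% (1-day events) and 100% (21-day events) of episodes. The durations and the uniform onset are assumptions. If cumulative rates were intended, the fault reduces to an undefined window, which still needs stating. On both readings the baseline test cannot inform safety. On the literal reading, early withdrawals because of adverse events may go uncounted. The change should be made, because the data for a better comparison are already being collected; the choice of a chi-squared test is not the problem.

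**What to change.** Replace the sentence in section 8.2 with wording such as: the proportion of participants with at least one adverse event from first dose to day 42 will be compared between arms among all who took study product, counting events that led to withdrawal, and reported as a risk difference with 95% CI, with an exact test where counts are sparse.

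Describe symptoms at baseline by arm without a test. Report events from the end-of-rotation query separately and descriptively, because they are not collected daily after day 42.

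The cost is one changed sentence and slightly more analysis work. No new data are needed: the daily questionnaire and the study nurse's follow-up, which records the nature, severity and duration of events, already supply them.
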